5. SAMPLE CALCULATION

5.1. First step:

For the safety analysis of the device, 25 women will be included, as advised by the National Ethics and Research Commission (CONEP).

5.2. Second stage:

The sample calculation assumed the premise of a cervical canal stenosis rate of approximately 15% to 20% after the CAF described in the literature and reduced to 6% with the use of an endocervical device according to the uncontrolled trial by Luesley et al (11) Considering this difference in stenosis rates (15-20% vs. 6%), an alpha error of 5%, a beta error of 20% and a balanced allocation 1: 1, the sample estimate ranges from 104 to 203 in each group. Therefore, this stage of the study will recruit 120 women in each arm, totaling 240 participants.

It is estimated that recruitment will take place between 1 to 3 weeks in the first stage and between

25 to 30 weeks in the second stage, since the potential for recruitment is 06 to 10 surgeries per week.

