1. INTRODUCTION

The term high-grade cervical intraepithelial neoplasia (CIN) is used to define lesions previously referred to as moderate dysplasia (CIN II) and severe dysplasia / in-situ carcinoma (CIN III) (1).

Literature reviews regarding the natural history of these lesions indicate that 43% of untreated NIC II lesions will regress in the absence of treatment, while 35% will persist and 22% will progress to in-situ carcinoma or invasive carcinoma (2). In comparison, 32% of NIC III lesions will regress spontaneously, 56% will persist and 14% will progress (1, 3).

The treatment of high-grade CIN (CIN II, III) is divided according to the patient's colposcopic evaluation. In cases of satisfactory colposcopy (visible squamous-columnar junction), both ablative and excisional methods are adequate (4). Ablative methods include cryotherapy, laser vaporization, electrocautery, diathermy, cold coagulation, while excisional methods include LEEP (excisional electrosurgical loop) also called High-Frequency Surgery (CAF), laser conization and cold conization.

It is important to emphasize that excision procedures allow a detailed assessment of all excised tissue, thereby reducing the risk that a micro-invasive lesion or occult invasive carcinoma is inadvertently treated as a pre-invasive lesion. When the colposcopic evaluation is unsatisfactory (squamous-columnar junction not visible) there is a chance of up to 7% of the diagnosis of occult invasive carcinoma in the conization specimen by a biopsy showing NIC II/III. Thus, diagnostic conization procedures that allow pathological examination of the tissue of the endocervical canal are usually used for women with biopsies confirming NIC II/III who have an unsatisfactory colposcopic evaluation.

The complications inherent to conization involve stenosis of the cervical canal, amenorrhea, dysmenorrhea and deep dyspareunia. (5)

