Participants whose anatomopathological report of the conization surgical specimen demonstrates invasive cervical carcinoma will have the device removed before the deadline and will be referred for appropriate cancer treatment.

The early removal of the device may be carried out if, after its placement, the researcher identifies potential risk to the research participant or also at the request of the same.

4.9 Study steps:

This is a study whose main objective is to evaluate the safety and effectiveness of a new therapeutic device. The study design foresees the realization of two distinct sequential steps. The first stage aims to determine the safety of using the DUDA device in initially 25 women. Concluding that the device is safe for the participants, we will proceed to the second stage, in which, in addition to safety, the effectiveness of the device in preventing post-conization endocervical canal stenosis (CAF) will be evaluated in a study randomized, open and parallel study with 240 women (120 in each arm). This study design aims to bring greater security to the research participants, avoiding recruiting a large number of women unnecessarily.

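### Section 5.2 derives 104 to 203 women per arm and concludes 120 without naming the control rate behind it; at the plan's own 15% versus 6%, power is about 64% or 55%, depending on the test, not 80%

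*Protocol*

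**What the plan says.** Section 5.2 (second stage) starts from "a cervical canal stenosis rate of approximately 15% to 20% after the CAF described in the literature", which it expects to be "reduced to 6% with the use of an endocervical device". The error rates and allocation are "an alpha error of 5%, a beta error of 20% and a balanced allocation 1: 1". From these it concludes: "the sample estimate ranges from 104 to 203 in each group. Therefore, this stage of the study will recruit 120 women in each arm".

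Section 4.9 repeats the size as a "study with 240 women (120 in each arm"), and section 4.9.2 also gives 240 women allocated 1:1. Section 6 compares stenosis rates between the groups by the chi-square test or Fisher's exact test, depending on the observed tables, at the 5% level. It does not say whether the chi-square test is continuity-corrected. The first footnote to the schedule table in section 10 puts 240 women in each arm, which disagrees with the other sections.

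**The concern.** A range of required sample sizes is a list of answers to different questions. Each value gives 80% power at one control rate only: 104 at 20% and 203 at 15%. Choosing 120 therefore amounts to choosing a control rate, but section 5.2 does not say which. It leaves beta 20% attached to the whole 15–20% premise and presents 120 as the consequence. At the 15% end, 120 is 203 − 120 = 83 women per arm short of the plan's own requirement.

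This paragraph is the protocol's only power justification for the primary objective. Ethics reviewers and the monitoring committee need to know under which control rates the trial has the power it states.

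**Working it through.** **Inputs, all from section 5.2.** Control rate p₁ = 0.15 to 0.20; device rate p₂ = 0.06; alpha 5%; power 80%; allocation 1:1; chosen size 120 per arm. Sidedness is not stated. Two-sided is used because it reproduces the stated range and one-sided does not.

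**Step 1: reproduce the plan's range.** With d = p₁ − p₂ and p̄ = (p₁ + p₂)/2:

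n = [1.960·√(2p̄(1−p̄)) + 0.842·√(p₁(1−p₁) + p₂(1−p₂))]² / d²

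n_cc = (n/4)·[1 + √(1 + 4/(n·d))]²

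- 20% vs 6%: n = (0.9322 + 0.3915)²/0.14² = 89.4; n_cc = 103.2, rounded up to **104**.
- 15% vs 6%: n = (0.8497 + 0.3609)²/0.09² = 180.9; n_cc = 202.6, rounded up to **203**.

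Both ends match exactly, so the plan used the continuity-corrected formula. Without the correction the range would be 90 to 181. The one-sided versions give 84 to 164 (corrected) and 71 to 143 (uncorrected).

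**Step 2: find the control rate for which 120 is the answer by that formula.**

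| Control rate | n_cc per arm |
| --- | --- |
| 15% | 202.6 |
| 17.5% | 138.7 |
| 18% | 130.1 |
| 18.7% | 119.4 |
| 20% | 103.2 |

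So 120 per arm is enough only from about 18.7%.

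**Step 3: exact power at 120 per arm.** For every pair of event counts (a, b), take the binomial probability of a among 120 at p₁ and of b among 120 at 6%, and add up the pairs at which the two-sided 5% test rejects.

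| Control rate | Uncorrected chi-square | Fisher |
| --- | --- | --- |
| 15% | 64% | 55% |
| 16% | 72% | 63% |
| 17% | 78% | 71% |
| 17.5% | 81% | 75% |
| 18% | 84% | 78% |
| 20% | 92% | 88% |

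At this size the continuity-corrected chi-square test gives the same figures as Fisher's test. Power crosses 80% at a control rate of about 17.3% (uncorrected chi-square) or about 18.4% (Fisher; 18.35% before rounding). Solving the plan's own formula for power at n = 120 and 15% vs 6% gives 54%, in line with the Fisher figure.

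**Step 4: sensitivity to losses.** Section 5.2 makes no allowance for women who cannot be evaluated. If 10% were lost (an assumption; 120 × 0.9 = 108 per arm), exact power would be 60% / 51% at 15% and 89% / 84% at 20% (chi-square / Fisher).

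**The case against.** The strongest defence is that 120 is a reasonable mid-range choice. Under the uncorrected chi-square test, 80% power is reached from about 17.3%, just below the 17.5% midpoint. That covers (20 − 17.3)/(20 − 15) = 54% of the stated range, and power averaged evenly over 15–20% is about 80%. The uncorrected formula at the midpoint asks for 122 per arm. The uncorrected test is also the likelier one if Fisher's test is kept for tables with an expected count below 5 (a common convention, not stated in the plan). At 15% vs 6%, about 120 × (0.15 + 0.06)/2 = 12.6 events per arm are expected, so Fisher's test would hardly ever be called for.

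Much of this stands. A reader might infer that 120 meets its target only in the top part of the range, or that power is 55% whatever the test. Neither holds for the uncorrected chi-square test. The less favourable figures still belong beside the others, because the plan's own sample-size formula is continuity-corrected and section 6 leaves the form of the chi-square test open.

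The defence does not rescue the sentence in section 5.2. The plan does not give the mid-range reasoning, and its own formula asks for 139 per arm at the midpoint.

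A second defence is that the plan prints 104 to 203 beside 120, so nothing is hidden. That is true, and section 5.2 nowhere claims 80% power at every rate in the range. The fault is that the conclusion does not follow and that its control rate is not named.

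A reader might also use the introduction's statement that "there is a chance of up to 7% of the diagnosis of occult invasive carcinoma" as a loss rate. It cannot serve as one. It is an upper bound for women with unsatisfactory colposcopy, entry is not restricted to them, and section 4.8 has the device removed and the woman referred without saying that she leaves the analysis.

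**Conclusion.** The point holds. The range of 104 to 203 is correct, but 120 per arm does not follow from it with beta 20% over the stated 15–20% premise. At 15% vs 6% the planned effect would be missed with probability about 36% (uncorrected chi-square) or 45% (Fisher or continuity-corrected chi-square), against the stated 20%. At 20% vs 6% power exceeds the target.

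These figures assume a two-sided 5% test done once, all 120 women per arm evaluable, and a device rate of 6%. Losses, or any alpha spent on the interim looks at 25%, 50% and 75% of recruitment, would lower them. The 15–20% and 6% are taken as given.

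A reader might go further and infer that the trial must enrol 203 per arm, or that a non-significant result is bound to be misread as an adequately powered negative. The documents support neither. A trial of 120 per arm can be justified if the control rate it rests on is stated, and no section says how a null result would be reported.

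Nor does the section 10 footnote show that 240 per arm was intended. Sections 4.9, 4.9.2 and 5.2 agree on 240 in total. The 170 devices budgeted in section 9 cover 25 + 120 = 145 women but not 25 + 240 = 265.

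**What to change.** Keep 240 women. In section 5.2, replace the sentence that concludes 120 with the power delivered, for example:

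*With 120 women per arm, a device-arm rate of 6% and a two-sided 5% test, power is 92% (uncorrected chi-square) / 88% (Fisher) for a control rate of 20%, 84% / 78% for 18%, and 64% / 55% for 15%. Power of 80% requires a control rate of at least about 17.3% (uncorrected chi-square) or 18.4–18.7% (Fisher / continuity-corrected formula), with all women evaluable.*

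Optionally add a row for 108 evaluable women per arm, labelled as an assumed 10% loss: 60% / 51% at 15% and 89% / 84% at 20%.

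Reconcile the first footnote to the schedule table in section 10 with 120 per arm.

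The cost is protocol wording only. No extra women are needed and the design does not change. The downside is that the stated power becomes less favourable.

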6. STATISTICAL ANALYSIS

The casuistry will be characterized by means of descriptive statistics. Quantitative variables will be described by means and standard deviation or median and 25-75 percentiles, depending on their distribution. Qualitative variables will be described using absolute and relative frequencies.

The rates of stenosis of the cervical canal will be compared between the groups at different times of observation from the moment 2-PO using the chi-square test or Fisher's exact test, depending on the values ​​observed in the contingency tables. Adverse events are characterized by means of absolute and relative frequencies, and inferences are made using a 95% confidence interval. The calculation of the scores of the domains of the FACT-Cx questionnaire will follow the guidelines of the manual of the organization FACIT (Functional Assessment of Chronic Illness Therapy). The scores will be compared between the groups at each moment of observation using the t-test or Mann-Whitney test, depending on the data distribution. In all statistical calculations, the level of significance considered will be 5%.

An interim analysis is foreseen in the transition from the first to the second stage of the study and when the casuistry of the second stage reaches 25%, 50% and 75% of the recruitment estimate.

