Endocervical canal stenosis (early and late) will be assessed through clinical information and physical examination at each visit to the hospital after surgery. The participant will be asked about menstrual flow and dysmenorrhea during anamnesis, which would indirectly show whether the endocervical canal is patent or not. In the physical examination, after viewing the cervix through specular examination, the doctor will check the permeability of the canal by introducing the hysterometer through the cervical canal. The difficulty of introducing the 2.5mm hysterometer through the channel will be noted according to the following scale:

The possible passage of the hysterometer?

( ) No difficulty

( ) Little / Moderate difficulty, however possible passage of the hysterometer

( ) Could not pass

4.10.3. Quality of life:

Quality of life questionnaires are used in clinical trials and include important outcomes such as postoperative pain and related symptoms. For these assessments, in the present study, the following instruments will be used:

a) Functional Assessment of Cancer Therapy - Cervix Cancer (FACT-Cx), version 4.0, in Portuguese (Annex 1).

b) Universal Pain Assessment Tools: comprises the Visual Analog Pain Scale (VAS), the Numeric Visual Pain Scale (EVN) and the Faces Pain Scale (EF) (Annex 2).

4.11. Study interruption rules:

Below are the study interruption criteria:

a) Registration of a single grade 5 adverse event at any stage of the study;

b) Record of two grade 3 or 4 adverse events in the first stage of the study;

c) Record of two grade 3 or 4 adverse events in the second stage of the study;

d) the benefit of using the device under interim analysis;

e) Identification of considerable risk to participants not provided in this research protocol.

In any of the aforementioned situations, the researcher, before interrupting the study, will communicate the Research Ethics Committee (CEP) of the Barretos Cancer Hospital and await the substantiated opinion, unless the risk to the participants is imminent. In the latter situation, the researcher will interrupt the study to safeguard the research participants and will communicate the CEP as soon as possible.

4.12. Study visits and data collection:

TABLE 1 summarizes the activities carried out in the study according to the time of the visits.

4.12.1. Baseline visit:

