At the time of the initial visit, preoperative tests (blood count, serum biochemistry, coagulogram, chest X-ray, electrocardiogram and pregnancy test) and pre-anesthetic evaluation of women in whom CAF is indicated will be checked. This preoperative assessment is done on a routine basis and does not include specific aspects of the study. Women who are eligible for CAF and meet the study's eligibility criteria will be invited to participate in the survey. Those who agree will sign the Informed Consent Form at the initial visit.

During this visit, demographic and clinical information will be collected through interviews and consultation of medical records (Annexes 3). At this time, the quality of life questionnaires will also be applied.

4.12.2. Operative and postoperative visits:

On the day of surgery, a form will be filled out with the data pertinent to the surgical procedure. (Annex 4).

Postoperative visits will take place 15 days (1-PO) and 30 days (2-PO) after surgery. (Annexes 5 and 6). The acceptable windows of opportunity for visits will be ± 3 days. During these visits, the participants will undergo a medical consultation, when anamnesis and gynecological physical examination will be carried out. They will also answer the quality of life questionnaires. Any adverse event will be recorded on a specific form each post-operative visit in accordance with the Common Terminology Criteria for Adverse Events v3.0 (CTCAE V3). (Annex 7).

Participants who have the DUDA device will have it removed during the 2-PO visit during the gynecological examination.

4.12.3. Follow-up visits:

Follow-up visits will take place 3, 6, 12 and 18 months after surgery (respectively FUP-1, FUP-2, FUP-3 and FUP-4) according to our flow chart described below. The acceptable windows of opportunity for visits will be ± 10 days. During these visits, participants will undergo a medical consultation, when anamnesis and gynecological physical examination will be performed, which will include the collection of material for cervical cytology, hysterometry to assess the permeability of the endocervical canal and colposcopy to visualize the squamocolumnar junction. The degree of permeability of the channel will be recorded in a specific form. During follow-up visits, quality of life questionnaires will also be applied and adverse events will be recorded and follow-up information will be collected (Annex 8-11).

4.12.4. Surgery information:

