8.7. Guaranteed access to the search result

As each participant will be accompanied on an outpatient basis (periodic visits) at the Barretos Cancer Hospital, not only because of the research but also because of their underlying disease (cervical intraepithelial neoplasia), at each visit the study doctor will perform a gynecological physical examination and speak to the participant about the existence or not of cervical stenosis. Thus, everyone will know, during the outpatient follow-up, if postoperative stenosis of the cervical canal occurred.

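### Section 6 compares stenosis visit by visit and has no rule for a woman whose earlier stenosis was opened, so a treated stenosis can count as no stenosis at the late visits

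*Protocol*

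**What the plan says.** Section 3.1 sets the primary objective as the effectiveness of the device in preventing late stenosis.

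Section 4.10.2 sets out the assessment: "Endocervical canal stenosis (early and late) will be assessed through clinical information and physical examination at each visit to the hospital after surgery". The test is physical: "the doctor will check the permeability of the canal by introducing the hysterometer through the cervical canal". It has three grades: no difficulty, "Little / Moderate difficulty, however possible passage of the hysterometer", and a lowest grade for an instrument that would not pass.

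On timing, Section 4.12.3 states: "Follow-up visits will take place 3, 6, 12 and 18 months after surgery". Each of these visits includes "hysterometry to assess the permeability of the endocervical canal and colposcopy to visualize the squamocolumnar junction".

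Section 8.7 adds that at each visit the study doctor will "speak to the participant about the existence or not of cervical stenosis".

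Section 6 gives the analysis: "The rates of stenosis of the cervical canal will be compared between the groups at different times of observation", starting at the 30-day visit (2-PO), by chi-square or Fisher's exact test. It names no deciding visit, does not say whether a rate is the rate at a visit or by a visit, and gives no rule for a woman already found stenosed. The protocol does not say whether a stenosis found in follow-up is treated, or how a treated one is counted.

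**The concern.** Preventing stenosis and having an open canal on the day of a visit are different outcomes once a stenosis can be opened in between. Suppose a woman's canal cannot be passed at 6 months, is then opened by some procedure, and is passable at 12 and 18 months. Under separate visit-by-visit comparisons she is a case at 6 months and a non-case at 12 and 18. Those late visits bear on the primary objective, yet the device did not prevent her stenosis.

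The protocol makes such a course plausible. Every stenosis is looked for at four scheduled hysterometries, and the woman is told the result. Section 1.1 calls stenosis the most important complication of conization, lists serious consequences and refers to published treatment techniques. Nothing bars treatment during the 18 months.

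At stake is what the late comparison means. It would mix the effect of the device with the effect of whatever was done to women found stenosed.

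**Working it through.** **Inputs.** From Section 5.2: control rate 15% to 20%, device rate 6%, alpha 5%, power 80%, 1:1 allocation, 104 to 203 per arm estimated, 120 per arm planned. Assumed, because the protocol gives no figure: f, the share of all stenoses that have been opened and are found patent at the deciding late visit.

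**The plan's own figure.** With d = p1 − p2 and p̄ their mean:

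n = [1.960·√(2p̄(1−p̄)) + 0.842·√(p1(1−p1) + p2(1−p2))]² / d²

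n′ = (n/4)·[1 + √(1 + 4/(n·d))]² (continuity correction)

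- 20% v 6%: n = 89.4, n′ = 103.2, rounded up to 104.
- 15% v 6%: n = 180.9, n′ = 202.6, rounded up to 203.

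Both ends of the stated range reproduce, with a two-sided test and continuity correction.

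**Equal opening in both arms.** The late rates become p1(1−f) and p2(1−f), and the difference becomes d(1−f). At 20% v 6% and 120 per arm, the expected late cases are 24 v 7.2 at f = 0, 18 v 5.4 at f = 25%, and 12 v 3.6 at f = 50%.

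Exact power below sums binomial probabilities over all tables in which the uncorrected chi-square rejects at two-sided 5%. The normal approximation is given as a check where it was run.

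| f | Late rates | Difference (points) | Exact power | Normal approx. |
|---|---|---|---|---|
| 0 | 20% v 6% | 14 | 91.7% | 90.2% |
| 10% | 18% v 5.4% | 12.6 | 88.3% | – |
| 25% | 15% v 4.5% | 10.5 | 81.6% | 78.7% |
| 50% | 10% v 3% | 7 | 62.6% | 59.6% |
| 0 | 15% v 6% | 9 | 64.3% | 62.5% |
| 10% | 13.5% v 5.4% | 8.1 | 59.7% | – |
| 25% | 11.25% v 4.5% | 6.75 | 51.6% | 49.2% |
| 50% | 7.5% v 3% | 4.5 | 34.5% | 34.5% |

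Counting opened stenoses as cases restores the f = 0 rows.

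**Unequal opening** (normal approximation, starting from 90.2% for 20% v 6%):

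- Half of control stenoses opened, none in the device arm: 10% v 6%, power 20.6%.
- Half of device-arm stenoses opened, none in control: 20% v 3%, power 98.8%. The device then looks better than it is.

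**Cost of the alternative, ever stenosed at any visit.** Assume a false failure to pass occurs independently with probability e at each of the four visits, equally in both arms. A woman without stenosis becomes a case with probability g = 1 − (1−e)⁴, and each rate becomes p + (1−p)g. For e = 1%, 2% and 3%, g is 3.9%, 7.8% and 11.5%. Exact power for 20% v 6% is then 82%, 72% and 63%, against 89%, 87% and 84% if only one late visit is used. For 15% v 6% it is 49%, 40% and 33%, against 60%, 56% and 52%.

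**The case against.** The strongest reply is that no section says a stenosis found in follow-up is opened, so f has no anchor. At f of 5% to 10%, exact power for 20% v 6% falls only from 92% to 90–88%. A stenosis first seen at the deciding visit cannot have been opened before it, which limits f further; Section 1.1 notes that diagnosis can come as late as 28 months. An early closure still counts at the visit where it was seen. A rate at different times could also mean a rate by each time, and current status at a late visit has clinical meaning. Finally, carry-forward rules are often left to a statistical analysis plan, which is not shown.

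Most of this stands as a limit on size. It does not supply the missing rule: the protocol fixes the visit-by-visit comparison as its only efficacy analysis, and that leaves a treated stenosis as a late non-case.

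The documents do not support several stronger inferences:

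- **Passing the hysterometer itself opens the canal.** The protocol does not say so. A closed canal is recorded as one that the instrument could not pass, and passage with difficulty is never defined as stenosis.
- **The analysis is biased against the device.** That direction needs similar opening in both arms. Section 4.1 says the doctor is not blind, so opening could differ by arm.
- **The primary endpoint must be ever stenosed at any visit.** The objective is late stenosis, and false failures of 1% to 3% per visit would cost about as much power as 25% to 50% opening.
- **Assessments after a later excision or cancer treatment should be excluded.** That would condition on events after randomisation. The protocol describes no later excision in follow-up and does not say that women referred for cancer treatment (Section 4.8) are counted at later visits.
- **The follow-up forms lack the needed field.** Annexes 8 to 11 are not shown.

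**Conclusion.** The point holds in a limited form. Section 6 has no counting rule for a stenosis that was found and then opened, and on the natural reading such a woman is a non-case at the late visits on which the primary objective turns.

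The effect could be small or large. With equal opening in both arms, exact power for 20% v 6% falls from 92% to 88% if 10% of stenoses are opened and to 63% if half are. For 15% v 6% it falls from 64% to 60% and 34.5%. These figures rest on the protocol's own rates, 120 evaluable women per arm, an uncorrected chi-square test and an assumed f. The low starting power at 15% is a sample-size matter and not part of this point. With unequal opening the direction is open. The rule should be set in advance, because the size of f cannot be known now.

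**What to change.** In Section 6:

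1. Name the late visit at which the primary comparison is made.
2. Count as a case at that visit any woman with stenosis then, or with an earlier recorded stenosis followed by any procedure to open the canal.
3. Report cumulative (ever-stenosed) rates by arm as a sensitivity analysis.
4. Keep the visit-by-visit rates as description.

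Check that the follow-up data capture any canal-opening procedure and its date, and add an item if they do not.

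The cost is a few sentences and at most one item of data, with no new visits or participants. The rule governs counting only and leaves the decision to treat a stenosis untouched. One small downside: a woman treated for a narrowing that might have resolved by itself counts as a case.

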3. OBJECTIVES

3.1. Primary objective:

To evaluate the effectiveness of a new cervical device called DUDA in preventing late cervical canal stenosis in women undergoing conization with a high-frequency scalpel.

3.2. Secondary objectives:

3.2.1. Assess the safety of using the device;

3.2.2. Compare the quality of life in women with and without the device after surgery;

3.2.3. Compare the rate of visualization of the squamous-columnar junction (JEC) in women who used the device or not (3 and 6 months after surgery);

3.2.4. Describe menstrual periods in women who used device placement after surgery.

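### Section 6 tests the FACT-Cx domain scores between arms at every visit, each at 5%, with no deciding score or visit and no exploratory label, so a chance quality-of-life finding is common

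*Protocol*

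**What the plan says.** Objective 3.2.2 of the protocol is to "Compare the quality of life in women with and without the device after surgery". It is one of the secondary objectives; the single primary objective concerns late stenosis.

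Section 6 turns this into tests. It refers to several scores ("The calculation of the scores of the domains of the FACT-Cx questionnaire") and continues: "The scores will be compared between the groups at each moment of observation using the t-test or Mann-Whitney test, depending on the data distribution". Its rule on level is general: "In all statistical calculations, the level of significance considered will be 5" per cent.

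The visits are fixed in Sections 4.12.2 and 4.12.3: "Postoperative visits will take place 15 days (1-PO) and 30 days (2-PO) after surgery", and "Follow-up visits will take place 3, 6, 12 and 18 months after surgery". Questionnaires are answered at all six. The schedule-of-activities table in Section 4.12 also marks quality of life at baseline and on the day of surgery, which makes eight moments.

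The protocol names no domain, total score or visit as the one that answers objective 3.2.2. For these comparisons it gives no testing order, no division of the 5%, no global test and no exploratory label.

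**The concern.** One question about quality of life is answered by a grid of domain-by-visit tests, each at the full 5%. Nothing says how many significant cells, or which ones, would count as an answer.

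Two features of this trial make that matter. First, the device is in place until the 30-day visit and is out from 3 months on. Early and late comparisons therefore address different things and could point in opposite directions. Objective 3.2.2 says only that the comparison is after surgery, so either period could be quoted as its result. Second, the trial is open and the scores are self-reported, so it is useful to settle in advance how an isolated difference will be read.

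A literal reading of Section 6 also takes in baseline, before any device has been placed. A between-arm test there cannot show a device effect.

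**Working it through.** **Plan's own figure.** The protocol states no sample size or overall error rate for quality of life. The only relevant figure is the 5% level per test.

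**Inputs from the protocol**
- Level per test: 0.05 (Section 6), taken as two-sided.
- Visits after surgery with questionnaires: 15 and 30 days, and 3, 6, 12 and 18 months, so 2 + 4 = 6. Baseline is left out because it cannot reflect the device. The day of surgery is left out because objective 3.2.2 concerns the time after surgery.

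**Assumptions, because the protocol does not give them**
- Number of domain scores: four or five. One score is shown as the lower bound.
- Correlation between test statistics: 0 to 0.7.
- The three pain scales in Section 4.10.3 are not counted. Testing them as well would raise the rates.

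**Step 1: number of tests.** One score: 1 × 6 = 6. Four domains: 4 × 6 = 24. Five domains: 5 × 6 = 30. The expected number of false positives with no true effect is 24 × 0.05 = 1.2 or 30 × 0.05 = 1.5, whatever the correlation.

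**Step 2: independent tests.** P(at least one p<0.05) = 1 − 0.95^k.
- k = 6: 1 − 0.95^6 = 26.5%
- k = 24: 1 − 0.95^24 = 70.8%
- k = 30: 1 − 0.95^30 = 78.5%

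**Step 3: correlated tests.** With a common correlation ρ between all k test statistics,

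P = 1 − ∫ φ(u) [Φ((1.96 − √ρ·u)/√(1−ρ)) − Φ((−1.96 − √ρ·u)/√(1−ρ))]^k du.

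Numerical integration gives:

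| Tests | ρ = 0 | ρ = 0.3 | ρ = 0.5 | ρ = 0.7 |
| --- | --- | --- | --- | --- |
| 1 score × 6 visits | 26% | 24% | 21% | 16% |
| 4 domains × 6 visits | 71% | 59% | 46% | 31% |
| 5 domains × 6 visits | 79% | 66% | 51% | 34% |

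**Step 4: a different correlation structure.** Two different domains at two different visits are probably less correlated than two domains at the same visit. If the between-domain and between-visit correlations multiply, simulation gives:
- Four domains: 53% (0.5 and 0.5) and 38% (0.7 and 0.7).
- Five domains: 60% (0.5 and 0.5) and 42% (0.7 and 0.7).

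These lie inside the range of Step 3.

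**Reading.** The lowest figure, one score with correlation 0.7, is about three times the stated 5% (16/5 = 3.2). The lowest figure for a set of domains is about six times (31/5 = 6.2). Whether the rate passes 50% depends on the assumed inputs. With five domains and a common correlation of 0.5 it is 51%; with four domains it is 46%.

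**The case against.** The strongest objection is that this belongs in the statistical analysis plan, which is not shown. Testing order and exploratory labels for secondary outcomes are often placed there, and a nominal 5% promises no control over a family of tests. That stands in part: a later plan could add such a rule. But the protocol is not silent. It specifies the test, repeats it at every moment and fixes one level for all calculations, so the sentence as written needs correcting.

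Next, quality of life is already secondary. The trial is sized on stenosis alone, and no stopping rule or success criterion rests on these scores. This stands, and it limits the severity.

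Several stronger readings are tempting, but the protocol does not support them:
- A reader might infer that a device with no effect would probably show a significant difference somewhere. That needs a domain count and correlations that the protocol does not give, and at strong correlation the rate falls well below 50%.
- A reader might count the day of surgery as a seventh moment, because the schedule table marks it. Section 4.12.2 describes only a surgical form that day, and the objective concerns the period after surgery.
- A reader might add two 5% tests for objective 3.2.3 ("Compare the rate of visualization of the squamous-columnar junction (JEC) in women who used the device or not (3 and 6 months after surgery"). Section 6 names no test for that outcome, and the objective itself fixes its two visits.

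**Conclusion.** The point holds in a limited form. The protocol fixes domain-by-visit testing at 5% each, with nothing to say which result decides. With no true effect, the chance of at least one nominally significant result over six post-surgery visits is about 16% to 26% for one score. It is about 31% to 79% for four or five domains. The ranges rest on the assumed number of domains and on correlations from 0.7 to 0. They support calling a false quality-of-life difference common; they do not support calling it more likely than not in every case.

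The primary conclusion on stenosis does not depend on these tests. Severity is minor to moderate.

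**What to change.** In Section 6:

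1. State that the quality-of-life comparisons are exploratory, that they are reported as between-arm differences with 95% confidence intervals, and that no claim of benefit or harm rests on a single domain or visit.
2. Alternatively, name in advance one FACT-Cx score at one visit as the single quality-of-life comparison at 5%, and label all other scores and visits exploratory. Do not make this comparison conditional on the primary stenosis result. Section 6 compares stenosis at several times and defines no single primary test, so such a condition would have no clear trigger. It would also bar a confirmatory statement about quality of life whenever stenosis was not reduced.
3. For these scores, restrict the comparison to the moments after surgery, so that baseline is described and not tested.

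The cost is a few sentences. No data, visits or participants change, and every planned comparison can still be reported. The small downside is that an isolated significant domain or visit can no longer be presented as a confirmed effect.
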